### Aim 1 measures

#### 
Primary outcome.

Black girls will receive STI testing at the CBOs on day 1 of their workshops. Trained research study staff will collect urine specimens from each girl at CBO sites. Urine specimens are delivered to the University of Illinois in Chicago Hospital Health Sciences System laboratory by a courier service, where trained clinical staff process the specimens for STI testing. The results of the STI testing are posted to EPIC, an electronic health records system. STI testing results are abstracted from EPIC and stored in REDCap. Trained research study staff call girls to communicate their STI testing results. Girls create a code word at the time of specimen collection. Research study staff are trained to confirm the name, date of birth, and the code word to ensure results are not shared with unauthorized parties.

#### Secondary outcomes.

Girls and male caregiver dyads will complete baseline, 6-and 12-month assessments via self-report surveys through REDCap. Sexual behavior will be measured by condom use and the number of partners. As a part of Aim 1, we will explore the three constructs of the *Becoming a Sexual Black Woman* framework*,* using self-report surveys that capture constructs of phases of sexual development, protection, and stereotyped messaging and measures that reflect all three levels of influence (individual-, interpersonal-, societal- levels) as outlined in the HDRF Framework (Table 3).

**Table 3 pone.0320164.t003:** Aim 1 Measures for Black Girls and Male Caregivers.

Becoming a Sexual Black Woman Framework Constructs	Operational Measure	Person*	
		G	BMC
**Phases of Sexual Development (Individual level)**			
Age of first intercourse	Age of first intercourse (vaginal, anal, and oral)	x	
Pubertal development	13-item scale describing perceived pubertal timing in comparison to peers, strategies to protect bodies and SRH, conditions influencing perceptions of bodies and behaviors and spaces feel most protected	x	
Condom self-efficacy	13-item measure of likelihood of condom use in diverse scenarios	x	
Sexual risk behavior	32-items, ARBA self-report of sexual behavior, assesses drug and alcohol use during sex (α = .79)	x	
HIV/STI knowledge, attitudes, and beliefs	18-item measure assessing factual information about HIV transmission, diagnosis, and prevention (α = .77)	x	x
Emotion regulation	20-item measure of emotion regulation, externally oriented thinking, and the ability to identify and describe feelings (α = 0.70)	x	
Coping with adverse life events	28-items self-report measures effective and ineffective ways to cope with stressful life events (α = .70)		x
Resilience	6-item, Brief resilience scale (α = .71)	x	x
Colorism	7 items, Skin Color Satisfaction Scale (α = .71)		
**Protection (Interpersonal level)**			
Caregiver-girl relationship and attachment	16-item scale, Child’s Report of Parent Behavior Inventory (CRPBI) perceived relationships of caregivers and girls	x	x
Sexual communication	20-item measure of perceived quality and quantity of risk-specific communication (e.g., having sex, condoms, and AIDS) (α=.65-.87)	x	x
Family risk and protection	38-item assessing 6 number of subscales on Family Conflict, Attitudes toward Attachment, Prosocial Involvement, Attitudes toward Drug Use (α = .66–.76)	x	x
Gendered racial socialization for BW	63- item, Gendered Racial-Ethnic Socialization Scale (GRESS) for Black women scale, gendered racial-ethnic socialization messages from caregivers regarding their identities (α = .67–.96)	x	
**Stereotyped Messaging (Societal level)**			
Stereotyping	11-item, to assess the extent to which participants endorse the sexualized stereotypes about Black women, to reflect the hypersexual and promiscuous nature of stereotypes. (α = 0.93)	x	x
Sexual objectification	11 item, Interpersonal Sexual Objectification Scale, experiences with having bodies evaluated (α = 0.91)	x	
Justification of Violence Scale	27-item, extent to which participants condoned IPV toward women when they behave in stereotype-consistent ways, (α = .99) for female and (α = .99) male sample	x	x
Everyday discrimination	5-item, Everyday Discrimination Scale, discrimination in everyday activities (α = .77)	x	x
G = Girls and BMC = Black male caregivers			

### 
Aim 2 implementation measures

Aim 2 data will be generated from the environmental scan, direct observations (fidelity ratings), study notes from meetings, semi-structured interviews documenting CBO personnel experiences hosting IMAGE (Table 4), and surveys (Table 5) of the CBOs’ attributes. Perceptions of acceptability, feasibility, and appropriateness of IMAGE will be assessed during *Preparation* after the *Rollout* phases, as well as views regarding IMAGE ownership during the *Sustain* phase.

**Table 4 pone.0320164.t004:** Aim 2 EPIS-Informed Semi-Structured Qualitative Interview Questions.

Outer Context
• What are your support structures/who supports your CBO (i.e., inter-organizational coalitions and relationships between entities, government, and funders)?
Inner Context
• How has the implementation of IMAGE been at your CBO? *Probe*: Did IMAGE address the needs of CBO families? • Tell me about your experience hosting IMAGE at your facility. *Probes*: How easy or difficult was it to run IMAGE at your CBO? Did IMAGE impact your work for the CBO? • What did you like and dislike about the IMAGE program? *Probes*: What were some of the inconveniences, difficulties, and problems you experienced while running IMAGE? Were you provided adequate support to host IMAGE? • What barriers do you foresee in running IMAGE at your CBO? *Probe*: What ideas do you have to overcome those barriers?
Bridging Factors
• How would you describe the relationship between you and the IMAGE team at UIC? *Probes*: What would you want to change about IMAGE? Do you feel like IMAGE aligns with your CBO mission?
Innovation
• At the completion of the study, would you want to continue offering IMAGE at your CBO, why or why not? • Is there anything else you would like to share about your experience with IMAGE? *Probe*: Is there a question you wish I’d asked during this interview?

**Table 5 pone.0320164.t005:** Aim 2 CBO Personnel Surveys.

Implementation phase	
Prep	**Organizational readiness.** Organizational Readiness for Implementing Change (ORIC) 12 items measuring confidence, commitment, motivation, and determination in implementing new interventions [39]
	**Organization climate.** CBO climate related to stress, workload, strain, and staff frustration [40]
Rollout	**Implementation, adoption and feasibility.** Inquiring about initial impressions of IMAGE programming after site first implements [41]
Sustain	**Appropriateness, acceptability, reach, and maintenance.** Assessing progressed impressions of IMAGE Programming at the end of efficacy trial [41]

#### 
Prepare.

We will conduct a baseline assessment at each CBO to describe the inner settings, bridging (CBO and UIC partnership), and innovation factors (IMAGE fit within each CBO). Aligning with implementation theories, we will ask CBO personnel to complete the Organizational Readiness for Implementing Change (ORIC) [39]. ORIC includes 12 items that measure confidence, commitment, motivation, and determination in implementing IMAGE. CBO personnel will also complete an Organizational climate [40] assessment, which consists of measures related to stress, workload, strain, and frustration, as these individual factors may influence the capacity to implement IMAGE in each setting.

#### Rollout.

Each CBO liaison will meet with the study’s project director weekly to discuss implementation challenges, recruitment, enrollment, rollout, and retention. Trained IMAGE facilitators will rate treatment fidelity of sessions when they act as observers. They will complete measures of adherence (delivery as planned) and competence (quality of delivery) for each session. The fidelity forms contain yes/no questions, including whether facilitators followed the session script/outline, explained and demonstrated each activity, provided corrective feedback, maintained an appropriate pace, and were open, non-judgmental, and comfortable with participants. The IMAGE research team will review fidelity checklists after each session. Areas of concern will be addressed with each facilitator during weekly supervision, and the facilitator(s) will be re-trained to reach fidelity as observed through our described model.

#### Acceptability, feasibility, and appropriateness.

We will document Black girls’ and caregivers’ *attendance* (Day 1 and Day 2) to indicate feasibility and acceptability. We will also select a random sample of five girls and five caregivers who complete IMAGE at each of the six CBOs (n = 60) to participate in qualitative interviews to document their experiences with IMAGE (each will be paid $50). Following consent/assent, we will ask about feasibility, acceptability, appropriateness, strategies to improve attendance, and reasons to deliver IMAGE in other venues. CBO personnel will complete the Acceptability of Intervention Measure (AIM) [42], Intervention Appropriateness Measure (IAM) [43], and Feasibility of Intervention Measure (FIM) [43], at the end of *Rollout.* The AIM assesses whether IMAGE is agreeable or satisfactory, the IAM assesses the perceived relevance or fits with each CBO’s mission, and the FIM captures the extent to which IMAGE was successfully carried out. Higher scores indicate greater acceptability, appropriateness, and feasibility.

#### Sustain.

The Program Sustainability Assessment Tool (PSAT) [44] will be used to evaluate potential IMAGE sustainability. The PSAT will generate a summary report of sustainability at the CBO and help inform sustainability planning. Individual scales represent organizational support, funding stability, positive academic and community-based partnerships, organizational capacity, program evaluation and adoption, stakeholder communication, and strategic planning (Fig 1).

## 
Data analysis

### Aim 1 analysis

#### 
Data reduction and preliminary analyses.

We will create summary scores for (1) Black girl-male caregiver relationship (quality and attachment), (2) Black girl-male caregiver communication (quality and quantity), and (3) girls’ risk behavior and attitudes (sexual behavior and condom use) [10]. We will create two separate forms of the dependent variable for girls: a composite score comprised of multiple risk indicators and a set of individual indicators (e.g., non-condom use, number of partners). We will compare groups on baseline variables using ANOVA (continuous) and Chi-square tests (categorical) and control for potential confounding variables in subsequent regression analyses that are not balanced by baseline randomization.

#### General statistical issues.

We will use Bonferroni correction to adjust for multiple comparisons as we will analyze multiple outcomes. We will control for Type I error in the analysis of the secondary outcomes but not the primary outcomes to capture important findings that may be obscured from the conservative limits imposed by Bonferroni correction. We will explore whether girls’ sexual behaviors are related to potentially important covariates (e.g., pubertal status) and use regression models to test their effects. To evaluate the impact of Black male caregivers on girls, we will include BMC’s characteristics as covariates in the regression model for girls’ outcomes. We will use a similar approach to evaluate the impact of girls on BMC over time. Missing data will most likely occur because of subject attrition. Based on our intervention studies, we expect 70%-85% retention in both arms. We will evaluate associations between dose (1 vs. 2 sessions) and efficacy. Missingness complicates statistical analyses via biased parameter estimates, reduced statistical power, and degraded confidence intervals. Based on our prior research, we expect minimal missingness in the data collection, but we will consider the item and unit nonresponse. An analysis using only completers is generally valid, assuming data are missing completely at random, but it is inefficient because it discards data points observed for non-completers. We will use all available data and produce valid inferences under the assumption that data are randomly missing. We will quantify the potential bias of these inferences should we suspect missing data to be non-random.

**Compare IMAGE vs. FUEL**^**TM**^
**on STI incidence and risky sexual behavior:** We will evaluate treatment effects separately at 6- months and 12 months. We will also combine data to evaluate an average effect across both time points and to analyze the change from 6- to 12 months. We will analyze binary outcomes using logistic and continuous outcomes using linear regression. At a single time point, we will test the effect of the binary indicator for IMAGE vs. FUEL on the outcome, adjusting for confounders and the outcome at baseline as additional independent variables. We will use mixed-effects regression models to analyze the outcome by combining both time points, and we will include a random intercept term to account for intra-subject correlation. We will test an average effect across time points and effects on patterns of change from 6- to 12 months by including an interaction term between treatment and time. We will use survival analysis to examine sexual initiation over the course of the study. We hypothesize that non-sexually experienced girls in IMAGE will, on average, initiate sex later than FUEL participants. We will estimate the Kaplan-Meier survival curves and conduct long-rank tests to compare the two survival curves. We will use Cox regression models and its extensions (e.g., Cox’s Proportional Hazard Model with Time-Dependent Covariates) to test for the effects of other covariates such as age or socioeconomic status.

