#### Aim 1 (Efficacy).

We will assign 300 14-18-year-old Black girls and their male caregivers to workshops randomized to either IMAGE or FUEL and assess girls’ STI incidence, sexual partners, and condom use at baseline, 6- and 12-months. We hypothesize that girls who receive IMAGE will have lower STI incidence (primary outcome), fewer sexual partners, and more consistent condom use (secondary outcomes). We will explore associations of individual, interpersonal, and structural factors proposed by the B*ecoming a Sexual Black Woman* and HDRF framework on primary and secondary outcomes at all three time points (Fig 1).

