#### Randomization, sample size, and power.

We will use a stratified block randomization allocation to assign girl-BMC dyads to the treatment arm (IMAGE n = 150 or FUEL n = 150) prior to baseline assessment. Power analyses determined that a sample of 300 girls – 150 IMAGE and 150 FUEL is needed to assess efficacy on the primary outcome (STI incidence). Effect size (Cohen’s h) is a function of two proportions defined by Cohen; h = .2 is a small effect, h = .5 is a medium effect, and h = .8 is a large effect. We calculated the power to detect the effect of IMAGE vs. FUEL in reducing STI incidence as measured by having any of three STIs at 12 months post-intervention using a 2-sided test with alpha = .05. The new STI outcome at follow-up was a binary variable (yes/no to testing positive for at least 1 of the 3 STIs), because the study was not powered to examine specific STI outcomes. Based on the IMARA retention rate of 86% for Black female caregiver-girl dyads in Chicago [15], we evaluated the power of STI incidence (yes/no) at 80% retention over 12- months. Based on our previous work, we assume the STI incidence is 25% and 11% at 12 months for girls in the FUEL arm and IMAGE arm, respectively, which is a small-to-medium effect size of h = .37. With the proposed sample size, we will achieve 80% power to detect the intervention effect. We also calculated the standard effect size (Cohen’s d) for group mean comparisons with 80% power for our secondary continuous outcomes, where d = 0 is defined as no treatment effect. We can detect a small-to-medium effect size with the proposed sample size (d = .37).

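### Single-step Bonferroni for the secondary outcomes is valid but needlessly inefficient; Holm gives the same error control and rejects everything Bonferroni rejects

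*Protocol article*

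**What the plan says.** The General statistical issues section of the protocol article names the method: "We will use Bonferroni correction to adjust for multiple comparisons as we will analyze multiple outcomes". The next sentence sets its reach: "We will control for Type I error in the analysis of the secondary outcomes but not the primary outcomes". The reason given for leaving the primary uncorrected is a wish to capture "important findings that may be obscured from the conservative limits imposed by Bonferroni correction". The article mentions no stepwise version and gives no reason for using the single-step form on the secondaries.

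Aim 1 (Efficacy) names two secondary outcomes, number of sexual partners and consistency of condom use. The size of the corrected family is not stated. It could exceed two: the paragraph comparing IMAGE with FUEL says "We will evaluate treatment effects separately at 6- months and 12 months" and adds an average effect and a change between the two visits, and the data reduction paragraph adds a composite risk score.

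The sample size section gives the inputs for a power check: "IMAGE n = 150 or FUEL n = 150"; "we evaluated the power of STI incidence (yes/no) at 80% retention over 12- months"; for the primary outcome, "using a 2-sided test with alpha = .05"; and, for continuous secondary outcomes, a detectable d of .37 at 80% power.

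**The concern.** Bonferroni holds every test in the family to .05/m, where m is the number of tests. Holm holds only the smallest p-value to .05/m and relaxes the threshold after each rejection, with the same family-wise guarantee. The article hypothesises benefit on both named secondary outcomes. If both effects are real, single-step Bonferroni makes it more likely that one of them is missed, without a lower family-wise error limit in return.

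What is at stake is power on the secondary outcomes. The primary outcome, the effect estimates and the validity of the type I error control are not affected.

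**Working it through.** **Inputs.** From the sample size section: 150 per arm and 80% retention, so 150 × .80 = 120 analysed per arm; d = .37. Assumed, because the article does not state them: family-wise two-sided .05 for the secondaries (it is stated for the primary), m = 2 for the two named outcomes with m = 4 as a larger case, a true effect of d = .37, correlation 0 to .6 between test statistics, and independent girls.

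**The plan's own figures.** Primary: h = 2·asin√.25 − 2·asin√.11 = .371. The pooled two-proportion test with 120 per arm has 81.0% power, against 80% stated. Secondary: power = Φ(d·√(n/2) − z), with .37 × √60 = 2.866, and detectable d = (z + .842) × √(2/120).

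| Level per test | z | Power at d = .37 | Detectable d at 80% power |
|---|---|---|---|
| .05 | 1.960 | Φ(.906) = 81.8% | .362 |
| .05/2 | 2.241 | Φ(.625) = 73.4% | .398 |
| .05/4 | 2.498 | Φ(.368) = 64.4% | .431 |

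The stated d = .37 at 80% power is therefore reproduced at the unadjusted .05, not after the Bonferroni correction.

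**Why Holm rejects everything Bonferroni rejects.** Order the p-values. Holm rejects in order while p(j) ≤ .05/(m − j + 1). If Bonferroni rejects r hypotheses, they are the r smallest, each with p(j) ≤ .05/m ≤ .05/(m − j + 1), so Holm rejects them too.

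**Why the error control is the same.** With m0 true nulls, the first true null that Holm could reject comes at step m − m0 + 1 at the latest, so it faces a threshold of at most .05/m0. By the Boole inequality the chance of any false rejection is at most m0 × .05/m0 = .05. No independence is needed.

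**Two outcomes, both real, independent.** Let a = .7339 (power at .025) and b = .8175 (power at .05).

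- Bonferroni: per outcome a = 73.4%; both a² = 53.9%.
- Holm: per outcome a + (b − a)·a = .7339 + .0837 × .7339 = 79.5%; both a² + 2a(b − a) = .5386 + .1228 = 66.1%.

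**With correlation** (simulated normal test statistics, 1,000,000 replicates per setting; at correlation 0 the simulation agrees with the exact values to about 0.1 point):

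| Correlation | Per outcome, Bonferroni → Holm | Both shown, Bonferroni → Holm | At least one, either method |
|---|---|---|---|
| 0 | 73.4% → 79.5% | 53.9% → 66.1% | 93.0% |
| .3 | 73.4% → 79.0% | 57.3% → 68.4% | 89.5% |
| .6 | 73.4% → 78.3% | 61.4% → 71.2% | 85.3% |

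**Where the gain is small or larger.**

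- One real effect of two, independent: the gain on the real one is (b − a) × .025 = .0837 × .025 = 0.2 points. At correlation .6 it is 0.1.
- Both effects d = .2, correlation .3: 24.4% → 27.2%, or 2.8 points.
- Four tests, two real: 64.3% → 66.9% (independent), about 2.5 points.
- Four tests, all real at d = .37: 64.3% → 75.2% (independent) and 64.3% → 74.0% (correlation .3). At correlation .6 the gain is 8 to 9 points.

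In every simulated setting with a true null, the family-wise error of Holm was at most .0496, and no replicate had a Bonferroni rejection that Holm missed.

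**The case against.** The strongest reply is that Bonferroni is a valid and familiar method, so this is a reviewer's preference and not an error. That stands in part: no inference becomes invalid, and the procedure errs on the safe side. But the article does fix the method, and another method with the same guarantee never does worse on the tests.

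A second reply is that a condensed article leaves detail to the analysis plan. That applies to the family and its size, which are not criticised here. It does not apply to the choice of correction, which is stated.

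A third reply is that the gains are a favourable case, because d = .37 is the detectable effect and not an expected one. This stands, and is why the small-gain scenarios are shown.

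A reader might also infer three stronger things that the documents do not support:

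- *That the plan calls Bonferroni too conservative for the secondaries and so contradicts itself.* The remark about conservative limits explains only why the primary is exempt. The plan accepts that cost for the secondaries.
- *That power is given up for nothing.* Bonferroni has simple matching simultaneous confidence intervals and Holm does not. The plan does not cite this as its reason, but it is a real advantage.
- *That correlated outcomes are where Holm gains most.* At d = .37 the per-outcome gain shrinks as correlation rises, from 6.1 points at 0 to 4.9 at .6. What drives the gain is several effects being real.

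**Conclusion.** The point holds as a cheap improvement confined to the secondary outcomes. Single-step Bonferroni is valid, and Holm is at least as powerful at the same family-wise level whatever the family size or dependence, provided that each p-value is itself valid.

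For the two named outcomes the per-outcome gain runs from almost nothing (one real effect) to about 5 to 6 points (both real at d = .37), with 10 to 12 points on showing both. It would be about 8 to 11 points per outcome for four tests that are all real, but the article does not state such a family. The sizes rest on the assumed effects, correlation, family size and 120 independent girls per arm; that Holm never rejects less does not.

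**What to change.** In General statistical issues, replace Bonferroni correction with the Holm step-down procedure at family-wise two-sided .05, over the same secondary family, and report Holm-adjusted p-values. Make the change before any outcome data are seen, including at the interim analysis mentioned under Data monitoring. Study status puts recruitment at an early stage (15 dyads at submission, some still to be contacted), so there is time.

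The cost is one phrase in the plan and one line of code, with no extra participants or data. The downside is the lack of simple matching simultaneous intervals. If Bonferroni intervals are kept, state in advance that they may include the null for an outcome that Holm rejects. With two outcomes this happens when the larger p-value lies between .025 and .05 and the smaller is at most .025, which is exactly where Holm gains.

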#### Aim 1 efficacy trial.

Six to eight dyads will be assigned to workshops randomized into FUEL or IMAGE at each CBO and will receive the corresponding curriculum on a designated weekend. Four facilitators and two observers are needed for each study condition; facilitators are not to be cross-trained in IMAGE and FUEL. Two facilitators co-lead the girls’ groups, and two co-lead the male caregivers’ groups. All four facilitators co-lead the joint sessions when girls and male caregivers come together for specific activities. Breakfast, lunch, and snacks are provided at all workshops for facilitators and participants.

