#### Contamination.

We will minimize contamination across arms. Facilitators will be assigned to IMAGE or FUEL and will not discuss or learn the other arm’s curriculum; training is done separately. The workshops will not be conducted on the same days; weekends will be divided, and each CBO will have only FUEL or IMAGE weekends to reduce participant contact. Confidentiality and a general orientation to the research structure were emphasized during facilitation training, allowing us to expect limited contamination.

### Intervention: 3-step sequence for implementation aim 2

We will utilize a 3-Step Implementation Model and its implementation guide [33] at each CBO to Prepare, Rollout, and equip them to Sustain IMAGE. The three steps are outlined more in the implementation procedures section.

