### Step 2 rollout

Each CBO hosts an equal number of IMAGE and FUEL workshops for the efficacy study (Aim 1).

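### Workshops of six to eight dyads are described as the randomised unit, but the 80% power and the Aim 1 models treat girls as independent; the size of the error depends on an intraclass correlation that is not given

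*Protocol article*

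**What the plan says.** The protocol article gives two accounts of what is randomised. Its Design section and its Aim 1 (Efficacy) section have dyads placed into workshops and the workshops randomised. The Aim 1 efficacy trial section agrees: "Six to eight dyads will be assigned to workshops randomized into FUEL or IMAGE at each CBO". The section on randomization, sample size, and power instead describes a "stratified block randomization allocation to assign girl-BMC dyads to the treatment arm".

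Delivery is by group on either account. A workshop is a weekend programme for six to eight dyads, led by four facilitators who are trained in one curriculum only.

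The power statement rests on two proportions: "we assume the STI incidence is 25% and 11% at 12 months for girls in the FUEL arm and IMAGE arm, respectively". It tests them "using a 2-sided test with alpha = .05", takes 150 girls per arm and 80% retention, and concludes: "With the proposed sample size, we will achieve 80% power to detect the intervention effect". It mentions no ICC or design effect.

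The analysis section comparing IMAGE with FUEL plans logistic or linear regression at each visit, with arm, confounders and the baseline outcome. For both visits together it plans a mixed model: "we will include a random intercept term to account for intra-subject correlation". No Aim 1 model, including the survival and mediation analyses, names workshop, facilitator or community-based organisation (CBO).

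**The concern.** Girls in one workshop share a discussion group, a facilitator team and a weekend, so their later outcomes may be correlated. If the workshop is also what is randomised, the number of independent units is about 38 to 50 workshops (300/8 to 300/6), not 300 girls. Standard errors that ignore this are too small when the correlation is positive, and the nominal 5% level of the primary test no longer holds. A test that does account for it has less power than the independent-girls calculation gives.

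The subject-level intercept is right for repeated measures. The fault is that it is the only correlation term stated. The conflict over the randomised unit matters too, because the valid analysis depends on which account is true.

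**Working it through.** **Inputs from the protocol article (Randomization, sample size, and power; Aim 1 efficacy trial).** Incidence 25% (FUEL) and 11% (IMAGE); two-sided alpha 0.05; 150 per arm; 80% retention, so 150 × 0.80 = 120 analysed per arm; 6-8 dyads per workshop.

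**Assumptions.** The ICC is not given, so 0.01 to 0.10 is used. Workshop size is taken as 7 dyads, so m = 7 × 0.80 = 5.6 analysed girls.

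**Step 1: reproduce the stated power with no clustering.** h = 2·arcsin√0.25 − 2·arcsin√0.11 = 0.371, which matches the stated .37.
- Arcsine formula: power = Φ(0.371·√(120/2) − 1.96) = 82.0%.
- Pooled two-proportion formula at 120 per arm: 81.0%.

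The 80% claim therefore reproduces as a comparison of independent girls, with almost nothing to spare.

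**Step 2: the margin.** For 80% power the arcsine formula needs 2·(1.96 + 0.842)²/0.371² ≈ 114 per arm, and the pooled formula needs 118 after rounding up. With design effect DE = 1 + (m − 1)·ICC = 1 + 4.6·ICC:
- Arcsine: 120/114 = 1.053, so the margin is gone at ICC = 0.053/4.6 ≈ 0.011.
- Pooled: 120/118 = 1.017, so it is gone at ICC = 0.017/4.6 ≈ 0.004. Without rounding, the requirement is 117.03, and (120/117.03 − 1)/4.6 ≈ 0.006.

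**Step 3: size over the assumed ICC range.** Effective n per arm = 120/DE. True alpha of a nominal 5% test that ignores workshops = 2·(1 − Φ(1.96/√DE)). Power is for a test at a true 5% level, from the Step 1 formulas at the effective n.

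| ICC | DE | Effective n per arm | True alpha | Power, pooled | Power, arcsine |
|---|---|---|---|---|---|
| 0.01 | 1.046 | 114.7 | 5.5% | 79.2% | 80.2% |
| 0.02 | 1.092 | 109.9 | 6.1% | 77.5% | 78.5% |
| 0.05 | 1.230 | 97.6 | 7.7% | 72.4% | 73.6% |
| 0.10 | 1.460 | 82.2 | 10.5% | 64.9% | 66.2% |

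A t reference with degrees of freedom equal to workshops minus 2 (about 41) lowers the arcsine power by about 2 points.

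**Step 4: sensitivity to workshop size.** With 6 or 8 dyads, m is 4.8 or 6.4. At ICC 0.05, DE is then 1.19 or 1.27, true alpha 7.2% or 8.2%, and power 74-75% or 71-72%. With only 3 analysed girls per workshop, DE at ICC 0.05 is 1 + 2 × 0.05 = 1.10, true alpha 6.2% and power 77-78%.

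**The case against.** The strongest objection is that the harm is conditional. The document gives no ICC, and at 0.01 the loss is about two points of power and half a point of alpha. On the arcsine formula, an ICC below about 0.011 leaves the 80% claim true. This stands. A reader might infer that the trial is materially underpowered, but the documents do not show that.

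Second, workshops may be smaller than planned. The Study status section reports four workshops held and 15 dyads enrolled or awaiting contact. The count is ambiguous, but if it covers those workshops, the average is below 4 dyads and the effect shrinks, as Step 4 shows. Adjustment for baseline outcome may also remove some correlation. Both points bear on size, not direction.

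Third, if dyads are individually randomised, only correlation arising from group delivery remains, and the alpha column is not shown to apply. This also stands. That correlation can still occur, so the workshop term is still warranted.

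Fourth, cluster terms are often left to the analysis plan. This does not carry the point, because the article itself states a power figure that leaves no room for a design effect, and itself sets out the model structure.

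Two stronger readings should be resisted. The Contamination section says "each CBO will have only FUEL or IMAGE weekends", from which a reader might infer one arm per CBO, with arm and site confounded. The context is scheduling, and Step 2 rollout rules that reading out: "Each CBO hosts an equal number of IMAGE and FUEL workshops". A reader might also infer that leaving CBO out of the models inflates type I error. With both arms equally represented in every CBO, site differences balance out and omitting CBO mainly costs precision. The ICC that matters is the correlation within workshops after CBO is allowed for.

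**Conclusion.** The point holds in conditional form. As written, the plan describes a group-randomised design in three sections, contradicts this in a fourth, and powers and analyses the trial as if girls were independent. If workshops are randomised, the direction is certain for any positive within-workshop correlation: p-values too small, and power below 81-82%.

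The size rests on assumed values, namely an ICC of 0.01 to 0.10 and 5.6 analysed girls per workshop. It runs from negligible (alpha 5.5%, power 79-80%) to serious (alpha 10.5%, power 65-66%). Confidence is high in the omission and the contradiction, and limited on the magnitude. Confounding of arm with site is no part of the point.

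**What to change.** 1. State one unit of randomisation, in the same terms, in Design, Aim 1 (Efficacy), the randomisation section and Aim 1 efficacy trial.
2. Add a workshop random intercept to every efficacy model, or use workshop-clustered robust standard errors with small-sample degrees of freedom. In the longitudinal model, place the workshop level above the girl's intercept.
3. Include CBO as a fixed effect, for precision.
4. Restate power over an assumed ICC range, such as 0.01 to 0.05, without changing the sample size, and accept that the figure may fall below 80%.
5. As a wording repair only, rephrase the sentence on FUEL and IMAGE weekends in the Contamination section so that it agrees with Step 2 rollout.

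The cost is protocol wording, one or two model terms and a recorded workshop identifier. No extra participants are needed. The price is a lower stated power: a point or two at the low end of the ICC range, and about 8 points below 80% at an ICC of 0.05 on the pooled formula (72.4%). Few dyads had been enrolled when the article was submitted, so the allocation rule can be settled while most recruitment lies ahead.
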